## Abstract

**Background:**

Opioid addiction and overdose are epidemic in the U.S. Victims of traumatic injury are at greater than average risk for opioid misuse and related complications. Potential risk screens and preventive interventions in this clinical population remain under-investigated. The current project seeks to develop and pilot the implementation of a screening tool for opioid risk at American College of Surgeons (ACS) Level I and Level II trauma centers.

**Methods:**

The project began with an online survey, which was sent to Wisconsin trauma center medical directors and trauma coordinators for the purpose of gathering information on current substance use screening practices. Next, a focus group of trauma center staff was convened to discuss barriers and facilitators to screening, resources available and needed to support trauma patients with opioid use disorders, and measurable clinical observations that could indicate a patient’s potential risk for opioid misuse. Data from the surveys and focus group were combined to inform the data collection instruments that are currently being administered to patients recruited from the University of Wisconsin Hospital Trauma Inpatient and Orthopedic Surgery Services. Eligible and consenting patients complete standardized measures of socio-demographics, substance use history, opioid misuse risk, mental health, medical history, and injury and pain severity. Follow up visits at weeks 4, 12, and 24 after hospital discharge assess hypothesized risk factors for opioid addiction and opioid use disorder diagnosis. At the completion of patient data collection, a forward stepwise regression will identify factors of most significant risk of the development of opioid use disorder after traumatic injury. This modeling will inform the development of a novel opioid risk screening tool, which will undergo pilot implementation at 4 Wisconsin ACS Level I and Level II trauma centers, using an evidence-based implementation strategy with roots in systems engineering.

**Discussion:**

Positive findings from the proposed work would lead to improved, standardized opioid risk screening practices among victims of traumatic injury. The ultimate goal of this and future work is to reduce the likelihood of opioid misuse, addiction, and related complications, such as overdose and death.

*Trial registration* Clinicaltrials.gov registration number: NCT02861976. Date of registration: Feb 9, 2016

**Electronic supplementary material:**

The online version of this article (10.1186/s13722-017-0097-6) contains supplementary material, which is available to authorized users.

## Background

Opioid use disorders and opioid overdose have reached epidemic proportions in the United States. Effective means to identify risk for opioid-related complications and interventions to prevent opioid use disorders and overdose deaths are, therefore, urgently needed. Nationally, approximately 1.5 million people aged 12 years and older received specialty treatment for heroin or other opioid use disorders in 2015 [1]. Between 2002 and 2011, admissions to substance-abuse treatment programs for prescription opioid use disorder rose by over 400% [2]. Yet, despite the rising prevalence of treatment, there were a record 20,101 deaths due to prescription pain reliever overdose in 2015, and an additional 12,990 deaths due to heroin overdose [3]. In Wisconsin (the geographic setting for the current project), treatment admissions for alcohol use disorder have remained relatively steady over the previous 10 years, while treatment admissions for heroin or other opioid use disorders increased more than 250%. The rate of treatment admissions for heroin or other opioid use disorder surpassed admissions for marijuana use disorder in 2008, and has since remained the most common illicit substance for which treatment is accessed in the state [4]. Yet again, despite the rising prevalence of treatment admissions, overdose deaths from heroin alone have increased more than 600% in Wisconsin since 2005.

Victims of traumatic injury are at greater than average risk for opioid use disorders and, therefore, represent a population with particular need for appropriate assessment, prevention, and intervention protocols; an area which remains severely under-studied. In one study of patients with a recent emergency room visit from which they were discharged with an opioid prescription, rates of misuse were 42% at either 3 or 30 days follow up [5]. In this study, 92% of the participants who reported misuse, reported self-escalation of the prescribed dose. Another study found that the rate of pre-injury opioid use for trauma patients is 16%, compared to 9% in the general population, indicating that pre-injury opioid use may be predictive of post-injury misuse [6].

Pain severity (and associated psychological distress) and pre-injury opioid use have been predictive of a greater duration of post-trauma opioid use [6, 7]. However, physical dependence and behaviors potentially indicative of a use disorder were not assessed in these investigations. Adolescent and young-adult initiates of opioid misuse who progress to injection opioid use frequently cite prescription of an opioid for an injury as their first exposure to opioid, and the event that led to their eventual addiction [8]. Alcohol is also a significant and well-recognized contributor to traumatic injury nationwide. Alcohol misuse predicted opioid misuse in a study of chronic pain patients [9], and was associated with nearly double the rate of opioid misuse (5.2% in low-risk drinkers compared to 9.8% in at-risk drinkers) in a sample of patients with traumatic injuries [7].

Despite this existing knowledge of some of the risk factors for opioid misuse, screening for opioid-related risk is not common practice at trauma centers, and systematic studies examining opioid use disorder screening and prevention in trauma populations have not been undertaken. Given the severity of the opioid addiction and overdose epidemic, such studies are urgently needed.

This study begins the crucial work of preventing opioid use disorder and overdose by developing and pilot testing a novel opioid risk screening tool and protocol. The long-term goal of this and future work is to provide trauma centers with the tools to both identify and prevent opioid misuse by disrupting the progression from prescribed opioid use to opioid misuse to opioid use disorder and related complications, such as overdose and death. Creating a screening tool for OUD risk identification is a necessary first step before designing processes to prevent and intervene with OUD risk in trauma settings, which we intend to do in future research. This work targets the population of traumatic injury victims because: (1) traumatic injury is a sentinel event that predicts subsequent opioid use, which simplifies identification of a group of at-risk individuals; (2) rates of opioid misuse and use disorder are twice as prevalent in post-trauma populations relative to the general population; and (3) opioid risk assessment is not systematically conducted on trauma services, and the feasibility and effectiveness of such a protocol remains under-investigated.

## Methods

### Primary aims

#### Aim 1

In a sample of traumatic injury victims (n = 295) at an American College of Surgeons, Level I trauma center, collect data on hypothesized risk factors for opioid misuse after traumatic injury, and monitor for the development of opioid use disorder during the 24 weeks follow up period.

#### Aim 2

Using the variables collected in Aim 1, develop a multivariate regression model of the proximal indicators that are most strongly associated with the development of opioid misuse or opioid use disorder (a composite outcome) after traumatic injury. Then, use this model to develop a parsimonious set of opioid risk screening items into a novel opioid risk screening tool which can be feasibly implemented at trauma centers.

#### Aim 3

Pilot test the implementation of the opioid risk screening tool at ACS Level I and II trauma centers in Wisconsin.

### Outline of data collection

To address Aim 1, preliminary data collection was necessary to inform the specific instruments and supplementary questions that would be administered to traumatic injury patients. First, an online survey was sent to Wisconsin trauma center medical directors and trauma coordinators to gather information on current substance use screening practices. Details regarding the procedures and results of these activities are attached in Additional file 1: Online Supplement 1. Next, a focus group of Wisconsin trauma center staff was convened to discuss barriers and facilitators to screening, resources available and needed to support trauma patients at risk for opioid use disorders, and measurable clinical observations that could indicate a patient’s potential risk for opioid misuse. Details regarding these procedures and results are attached in Additional file 2: Online Supplement 2. Finally, these data were used to finalize the items that are currently being administered to inpatients receiving trauma services (n = 295) at an ACS Level-1 trauma center in Wisconsin. In turn, these data will be analyzed and used for the development and validation of a screening tool for opioid use disorder risk after traumatic injury. The screening tool will be pilot-tested at four ACA Level-I and Level 2 II trauma centers in Wisconsin.

### Data collection from patients with traumatic injury

#### Sample, eligibility, and recruitment

Participants (n = 295) will be recruited from the UW Hospital Trauma Inpatient Service, which has an annual volume of 2000–3000 patients. Inclusion criteria are age 18–75 years, inpatient victim of traumatic injury, expected need for post-discharge outpatient opioid analgesia, English speaking, and post-discharge ability of participants to manage their own medications. Exclusion criteria are disposition to a skilled nursing or long-term acute care facility where medications are managed by people other than the participant, active opioid use disorder or current participation in a program of recovery for another substance use disorder, current cancer diagnosis, and inability to consent to research due to incapacitating injury or sedation. The electronic medical record (EMR) will be used for pre-screening Trauma Service inpatients for study eligibility. Potentially eligible patients will be offered information about the study. If clinical care staff confirms that the patient is able to provide consent for research and the patient is interested, they will complete an Informed Consent process. Final eligibility criteria will be assessed, including a computer-assisted diagnostic survey at baseline (the Composite International Diagnostic Interview-Substance Abuse Module) [10] to assess for existing opioid use disorder. Eligible patients will be enrolled in the study.

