### Primary outcome

The primary outcome is the development of opioid misuse or opioid use disorder during 24 weeks follow up, as measured by the Composite International Diagnostic Interview-Substance Abuse Module (CIDI-SAM) and/or the current opioid misuse measure (COMM).

The CIDI-SAM is a computer-assisted interview (average test–retest reliability *Κ* = 0.84) that identifies opioid use disorder presence and severity, based on symptom clusters, according to the 5th Edition of the Diagnostic and Statistical Manual of Mental Disorders. [10, 12, 13] The COMM is a 17-item paper survey with 5-point Likert scale response options, which will be used to identify the presence and severity opioid misuse behaviors. In order to determine changes in these behaviors over time, COMM will be administered at each follow up. The COMM has acceptable one-week test–retest reliability and internal validity (Intra-class Correlation Coefficient [ICC] = 0.86; 95% CI 0.77–0.92) [14, 15]. A raw score of greater than or equal to 9 will be considered positive for opioid misuse.

The composite outcome will be positive for participants with positive scores at week 24 on either the CIDI-SAM (opioid use disorder) or the COMM (opioid misuse), and will be negative for participations with neither.

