Alcohol Use Disorders Identification Test (AUDIT-C)	X			X
Composite International Diagnostic Interview-Substance Abuse Module for Opioid Use Disorder (CIDI-SAM)	X			X
Patient Health Questionnaire (PHQ-9)	X			
Generalized Anxiety Disorder (GAD-7)	X			
Opioid Risk Tool (ORT)	X			
Social Support Questionnaire (ISEL-12)	X			
Adverse Childhood Experiences (ACE)		X		
Brief COPE Inventory (COPE)		X		X
Current Opioid Misuse Measure (COMM)		X	X	X
Opioid Craving Scale (OCS)		X	X	X
Quality of Life Questionnaire (PROMIS)		X	X	X
Perceived Need Inventory (PNI)		X	X	X
Pain Intensity and Interference (PEG)		X	X	X
WI Circuit Court Access Program (CCAP)				X
WI Prescription Drug Monitoring Database (PDMP)				X

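### The misuse half of the primary composite measures misuse present at week 24, not its development, because misuse before the injury is neither excluded nor measured with the COMM at baseline

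*Protocol article*

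**What the plan says.** All references are to the Protocol article.

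- **Eligibility** (Sample, eligibility, and recruitment). The opioid- or substance-related exclusion is "active opioid use disorder or current participation in a program of recovery for another substance use disorder". The baseline CIDI-SAM is used "to assess for existing opioid use disorder". Misuse below the disorder threshold is not an exclusion.
- **Outcome label** (Primary outcome). "The primary outcome is the development of opioid misuse or opioid use disorder during 24 weeks follow up". Aim 2 under Primary aims and the analysis section for Aims 1 and 2 use the same idea. The sample size section calls the 8% an incidence, and the secondary survival analysis refers to incident misuse.
- **Measurement schedule** (Primary outcome and Table 1). The text says that "COMM will be administered at each follow up". Table 1 marks the COMM at weeks 4, 12 and 24 and leaves its baseline cell empty. The CIDI-SAM is marked at baseline and week 24.
- **Scoring** (Primary outcome). "A raw score of greater than or equal to 9 will be considered positive for opioid misuse". The composite is positive if either instrument is positive at week 24. Nothing in the rule refers to earlier status.
- **Prior use** (Background). One cited study found that "the rate of pre-injury opioid use for trauma patients is 16%, compared to 9% in the general population", and the article adds that such use may predict misuse after injury.

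**The concern.** To say that a condition developed during follow-up, a plan has to know who was free of it at the start. For opioid use disorder this plan does: the CIDI-SAM is given at baseline and active cases are excluded. For misuse it does not. A participant who misused opioids before the injury, fell short of a disorder, and still scores 9 or more on the COMM at week 24 counts as having developed misuse after trauma.

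Two uses of the data depend on this distinction. First, the analysis section wants variables that allow intervention before the onset of misuse. Univariate screening followed by forward stepwise selection cannot tell a predictor of new misuse from a marker of misuse already under way, and baseline measures such as the PMQ or ORT could enter the model for the second reason. Second, the time-to-event analysis of incident misuse has no verified misuse-free group at time zero.

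**Working it through.** **1. The passages side by side**

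| | Opioid use disorder | Opioid misuse |
|---|---|---|
| Instrument | CIDI-SAM | COMM, cut-off 9 |
| Measured at baseline | Yes | No |
| Present at baseline excluded | Yes, if active | No |
| Composite rule | Positive at week 24 | Positive at week 24 |
| What a week-24 positive shows | New since baseline | Present at week 24, onset unknown |

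The baseline PMQ and ORT bear on misuse, but the article lists them as independent variables. None of them defines who is at risk of new misuse.

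**2. The plan's own sample size**

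Inputs from the sample size section: event rate p = 0.08, odds ratio 2.0 per SD, 5% significance, 80% power, 25% drop-out.

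For logistic regression on one continuous covariate (Hsieh formula, two-sided):

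n = (1.960 + 0.842)² / [p(1 − p)(ln 2)²] = 7.849 / (0.08 × 0.92 × 0.4805) = 221.96

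This agrees with the stated 221; power at 221 is 79.8%. Recruitment is 221 / 0.75 = 294.7, rounded up to 295. The arithmetic is sound. What is open is what the 8% counts.

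**3. Expected events**

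221 × 0.08 = 17.7. Three persisting cases are 3 / 17.7 = 17% of these and four are 4 / 17.7 = 23%, so roughly 20%.

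**4. Illustration: a share f of the week-24 positives was already present before injury**

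f is not in the documents; the range is assumed. These cases are removed from both the events and the at-risk group. Power = Φ(√[n p(1 − p)] × ln 2 − 1.960).

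| f (assumed) | Persisting cases | New events | At risk | Power for OR 2.0 per SD |
|---|---|---|---|---|
| 0 | 0 | 17.7 | 221.0 | 80% |
| 10% | 1.8 | 15.9 | 219.2 | 76% |
| 20% | 3.5 | 14.1 | 217.5 | 71% |
| 30% | 5.3 | 12.4 | 215.7 | 66% |
| 50% | 8.8 | 8.8 | 212.2 | 52% |

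**5. Illustration: all prior users removed**

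Applying the Background's 16% to this cohort gives 0.16 × 221 = 35.4 prior users and leaves 185.6. Suppose 10%, 15% or 25% of them misused before injury and all of those still score positive at week 24 (both assumed). Then 3.5, 5.3 or 8.8 events are pre-existing, which is 20%, 30% or 50% of 17.7. Removing them leaves 14.1, 12.4 or 8.8 events among 185.6, and power of 71%, 65% or 52%. Any new events among prior users would be lost as well, so these powers are upper values under each assumption.

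**The case against.** The strongest case for the plan is that the tool is meant for the point of care, where patients with prior opioid use will also be screened. Enrolling them is a sound choice, pre-injury use is a legitimate candidate predictor, and misuse at week 24 is a reasonable target for screening. This stands, and it is why the full cohort should remain the primary analysis. It does not justify calling that target development or incidence.

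It can also be said that baseline information exists. That is true: the PMQ covers prescription use behaviours, the ORT is collected, and the CIDI-SAM records symptom clusters. The PMQ is a different scale from the COMM, however, and the plan uses none of these to separate existing from new misuse.

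A reader might infer three stronger points that the documents do not support:

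- **That the Aim 1 incidence is too high.** Aim 1 names only opioid use disorder, which is screened at baseline. Misuse enters with the Aim 2 composite and the 8%.
- **That 20% to 50% of events are pre-existing.** The 16% is use, not misuse, and comes from trauma patients in general, not a cohort with active use disorder excluded. The misuse shares and full persistence are assumed; if half persisted, the shares would halve to 10% to 25%. The 8% is also stated as a minimum.
- **That the primary model should be restricted to participants without prior use.** On the figures above, power would fall to between 71% and 52%, which is a real trade-off. Prescription fills show prescribed use, not misuse. Baseline MEDD reflects opioid use around discharge, in a cohort selected for expected outpatient opioid need, and could flag much of it.

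That misuse is the more frequent component is plausible, but the article gives no separate rates.

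**Conclusion.** The point holds for the misuse component only. Eligibility, the COMM schedule and the scoring rule together define misuse present at week 24, so *development*, *incidence* and *incident misuse* are not supported for it. They are supported for opioid use disorder. This conclusion rests on the text and on no assumed figure.

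The size of the effect is unknown, because the documents do not give the share of week-24 positives that predates the injury. What can be said is that about 18 expected events leave little room: three or four persisting cases would be about a fifth of them and could affect which variables are selected. The sample size itself reproduces and needs no change on this account. The correction matters because it changes what the study can conclude about new-onset misuse.

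**What to change.** 1. **Reword the outcome.** Keep the full cohort as the primary analysis and define the outcome as opioid misuse or opioid use disorder present at week 24. Drop *development*, *incidence* and *incident* for the misuse component in Aim 2, Primary outcome, the sample size section and the analysis section. The 8% becomes the expected proportion positive at week 24. Describe the survival endpoint as first detected misuse.
2. **Add a pre-specified sensitivity analysis.** Refit the model after excluding, or adjusting for, participants with evidence of pre-injury misuse from the baseline PMQ and sub-threshold baseline CIDI-SAM symptoms. Use pre-injury opioid use from EMR or PDMP records as a supporting proxy where the extract covers that period; the article does not say that it does. Do not use baseline MEDD as the flag. Report which selected predictors survive.
3. **Optional.** For remaining enrollees who report pre-injury opioid use, give the 17-item COMM at baseline with reference to the pre-injury period.

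Steps 1 and 2 cost wording and one further model on data already planned. The downside is that the sensitivity model has fewer events and lower power: about 71% or less for an odds ratio of 2.0 per SD if all prior users are removed, on the illustrative figures. It should be read for consistency with the primary model, not for significance. Step 3 adds one short paper form for roughly one in six remaining participants, if the 16% applies.

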#### Participant surveys

Baseline visits will be completed during the inpatient stay or within 1 week of discharge, with follow-up visits at weeks 4, 12, and 24 after hospital discharge. Surveys will assess sociodemographic characteristics and health characteristics hypothesized to predict opioid use disorder risk that are not available in the EMR. The baseline and 24-week survey must be completed in person. The 4 and 12-week follow-up surveys were designed to be completed via mail, in-person, or by telephone. If participants complete all 4 visits, they will be compensated a total of $150, to be disbursed in increments at each visit. All study data will be transcribed from hard-copy questionnaires and source documents into a secure, web-based application for storing, managing, and analyzing study data.

#### Administrative data sources

To assess hypothesized risk factors for opioid misuse or opioid use disorder, informed consent will give the study team permission to record personal health information from administrative records including the EMR, UW Health Trauma Registry, Wisconsin Circuit Court Access Program (CCAP), and Wisconsin PDMP Database. Administrative data sources include: emergency department notes and procedures from the EMR; Injury Severity Score (ISS) from the Trauma Registry [11], diagnosis codes from the EMR and trauma registry; concomitant medications, prescribed opioids, and other methods of pain management from the EMR and PDMP; and criminal activity from the CCAP. These data will be collected at week 24, at the conclusion of participant follow ups.

### Primary outcome

The primary outcome is the development of opioid misuse or opioid use disorder during 24 weeks follow up, as measured by the Composite International Diagnostic Interview-Substance Abuse Module (CIDI-SAM) and/or the current opioid misuse measure (COMM).

The CIDI-SAM is a computer-assisted interview (average test–retest reliability *Κ* = 0.84) that identifies opioid use disorder presence and severity, based on symptom clusters, according to the 5th Edition of the Diagnostic and Statistical Manual of Mental Disorders. [10, 12, 13] The COMM is a 17-item paper survey with 5-point Likert scale response options, which will be used to identify the presence and severity opioid misuse behaviors. In order to determine changes in these behaviors over time, COMM will be administered at each follow up. The COMM has acceptable one-week test–retest reliability and internal validity (Intra-class Correlation Coefficient [ICC] = 0.86; 95% CI 0.77–0.92) [14, 15]. A raw score of greater than or equal to 9 will be considered positive for opioid misuse.

The composite outcome will be positive for participants with positive scores at week 24 on either the CIDI-SAM (opioid use disorder) or the COMM (opioid misuse), and will be negative for participations with neither.

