### Statistical analyses

#### Aims 1 and 2: sample size calculations

Based on an expectation of an at-least 8% incidence in the sample over 24 weeks observation of opioid misuse or an opioid use disorder diagnosis, 221 participants would yield 80% power, at a 5% significance level, with a logistic regression to detect an odds ratio of 2.0 for a change of one standard deviation (SD) in score on the COMM. With a 25% drop-out rate expected, the study aims to recruit a total of 295 participants. While the current proposed work will not be adequately powered to attain significant findings regarding predictors of opioid overdose, examination of this outcome will constitute an exploratory aim.

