#### Aims 1 and 2: analysis

The primary outcome event of this study will be a composite outcome indicating the development or lack of opioid misuse or opioid use disorder within 24 weeks of hospital discharge after traumatic injury. To assess the associations between patient factors and hypothesized risk factors with primary event, t-tests, Wilcoxon rank sum tests, and Chi square tests will be applied to measures that differ between those participants who achieve the primary event and those who do not. The test that is used will be based on numeric (normal or non-normal distribution) or a categorical factor. Any baseline or week 4 variable that is univariately associated with the primary event (p < 0.05) and does not reduce the number of events by more than 5% due to missing data will be considered a candidate variable to be included in the development of a best fit prediction model. The prediction model will be constructed based on a forward step-wise logistic regression model building process with threshold for entry into the model of significantly improving the model at a 0.05 significance level. Including baseline and week 4 variables will allow knowledge of which baseline variables are associated with future opioid misuse or opioid use disorder, and which variables can indicate the beginning of addiction in the hopes to develop a method to intervene before the onset of opioid misuse or opioid use disorder. To control for a possible early drug effect, time-on-opioids will be used as a covariate in the model. The diagnostic ability of the model will be assessed by constructing a receiver operating characteristic (ROC) curve and calculating the optimal sensitivity and specificity to predict primary event based on Youden’s J statistic [34]. A secondary survival analysis will examine variables that are associated with time-to-event, such as overdose or incident misuse detected on study measures.

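### The primary composite gives no route to event status for a recorded opioid use disorder diagnosis or overdose without a positive week-24 score

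*Protocol article*

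**What the plan says.** The Primary outcome section opens with a period definition: "The primary outcome is the development of opioid misuse or opioid use disorder during 24 weeks follow up", measured by the CIDI-SAM and/or the COMM. The section Aims 1 and 2: analysis repeats the period idea: "development or lack of opioid misuse or opioid use disorder within 24 weeks of hospital discharge after traumatic injury". The sample size section likewise assumes an incidence accumulated across the 24 weeks.

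The scoring rule is a single-visit rule: "The composite outcome will be positive for participants with positive scores at week 24 on either the CIDI-SAM (opioid use disorder) or the COMM". The same sentence makes the composite negative by default: it "will be negative for participations with neither".

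Three other places bear on this:

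- Participant surveys: "The baseline and 24-week survey must be completed in person". Table 1 schedules the CIDI-SAM at baseline and week 24 only.
- Administrative data sources: emergency department notes and diagnosis codes are abstracted under consent, for the stated purpose of assessing risk factors. On timing: "These data will be collected at week 24, at the conclusion of participant follow ups".
- Overdose: the sample size section says that "examination of this outcome will constitute an exploratory aim", and the analysis section names overdose as an example of an event in the secondary survival analysis.

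**The concern.** Opioid use disorder and overdose are also the kind of events that can keep someone from an in-person visit at week 24. A participant who is diagnosed at week 10 and does not return, or who dies of an overdose, has no week-24 score. No earlier CIDI-SAM exists to fall back on. The article's period definition would count the recorded diagnosis, and arguably the overdose, as development of the condition. The scoring rule does not.

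The screening tool is built from this composite: the stepwise logistic model, the ROC curve and the Youden cut-off all use it. If documented cases are left out or coded negative, the tool is fitted to what people who attend report about themselves. The Abstract and Background give overdose and death as harms that this and future work is ultimately meant to reduce, so these are cases one would not want to lose by definition. The records that could identify some of them are collected, but are not assigned to the outcome.

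**Working it through.** **1. The plan's own figure.** Inputs from the sample size section: incidence p = 0.08, odds ratio 2.0 per SD, 80% power, 5% level (two-sided assumed; the article does not say), 25% drop-out. For logistic regression with one continuous normal covariate (Hsieh–Bloch–Larsen):

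n = (z₀.₉₇₅ + z₀.₈₀)² / [p(1 − p)(ln OR)²] = (1.960 + 0.842)² / (0.08 × 0.92 × 0.693²) = 221.96

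The article states 221, so this matches to rounding. Power at 221 is 79.8%. Then 221 / 0.75 = 294.7, giving 295. The sample size is not in error.

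**2. What one case weighs.** Planned events: 0.08 × 221 = 17.7. One event is 1 / 17.7 = 5.7% of these. As a yardstick, the analysis section bars a candidate predictor whose missing values would cost more than 5% of events, which is 0.05 × 17.7 = 0.9 of an event. That rule governs predictors, not outcomes, but it shows the loss the authors regard as material.

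**3. Where such cases could sit.** Expected drop-out is 0.25 × 295 = 73.75, about 74 people. Others may attend and score negative on both instruments despite a recorded event. The article gives no expected number of recorded diagnoses, overdoses or deaths in either group, so the count k below is an assumption.

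**4. Range for k.** Power = Φ(√[n p(1 − p)] × ln 2 − 1.96), with the odds ratio held at 2.0.

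| k | Share of planned events kept | Power if k of the planned events are coded negative (n = 221) | Power if k otherwise unassessed cases are added as events (n = 221 + k) |
|---|---|---|---|
| 0 | 100% | 79.8% | 79.8% |
| 1 | 94% | 77.7% | 81.8% |
| 2 | 89% | 75.4% | 83.6% |
| 3 | 83% | 72.8% | 85.2% |
| 5 | 72% | 66.9% | 87.9% |

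Example, k = 1: p = 16.68 / 221 = 0.0755; √(221 × 0.0755 × 0.9245) × 0.693 − 1.96 = 0.76; Φ = 0.777. Dropping the k cases instead of coding them negative changes power by about 0.1 point.

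The third column applies if the cases are among the 17.7 events planned for. The fourth applies if they are among the drop-outs already allowed for; planned power is then intact and the column shows what recovering them would add. Neither column includes any change in the odds ratio itself.

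**The case against.** **Overdose is not ignored.** It is an exploratory outcome and a named event in the secondary survival analysis. This stands, and confines the point to the primary composite. A reader might also infer that the overdose analysis can count only survivors who report it. The article does not support that: emergency notes and diagnosis codes are collected, and nothing restricts overdose to self-report. The link is simply not spelled out.

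**Counted negative is only one reading.** The article allows for 25% drop-out, which suggests that unassessed people are left out, and the rule for missing outcomes may be in the full protocol or analysis plan. This also stands. Under either reading, however, the recorded case is not an event.

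**Bias toward no association does not follow.** If missing outcomes are excluded and missingness depends only on the outcome, logistic odds ratios are unbiased and only the intercept shifts. Attenuation needs the negative coding, or missingness that also depends on predictors. The article shows neither, so the direction of bias is open.

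**The size is not known.** It is tempting to apply an assumed event rate to all 74 drop-outs and call the result lost severe cases. That would measure ordinary drop-out. The article expects too few overdoses for adequate power, and active opioid use disorder is excluded at baseline, so k may be small.

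**Two validated instruments are a defensible primary measure, and records bring their own problems.** Records can turn an unassessed person positive but never negative, no death registry is listed, and the diagnosis codes are meant as candidate risk factors. These objections stand. They favour a with-and-without analysis over silently replacing the primary definition. They do not remove the mismatch between the period definition and the single-visit rule, which the article itself states.

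**Conclusion.** The point holds for the primary composite. The scoring rule is narrower than the article's own definition of the outcome, and a recorded post-discharge opioid use disorder diagnosis or overdose without a positive week-24 score cannot become a primary event. A diagnosed participant who attends and scores positive is counted, so it would be wrong to say that severe cases in general are lost.

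Each such case equals about 6% of the planned events. If it would otherwise have been one of them, it costs about 2 to 3 points of power. This rests on the article's 8% incidence and 221 evaluable participants. The number of cases, and the direction and size of any bias in the predictors, cannot be derived from the article.

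**What to change.** - In Primary outcome, reconcile the period definition with the single-visit rule. Let a participant be negative only with a completed week-24 assessment, neither score positive, and no record of a post-discharge opioid use disorder diagnosis or opioid overdose.
- Pre-specify an analysis in which an EMR-recorded opioid use disorder diagnosis or opioid overdose, fatal or non-fatal, after discharge and within 24 weeks counts as an event whether or not the week-24 visit takes place. Report the prediction model and ROC results with and without these events.
- Do not offer the same EMR codes as candidate predictors.
- Name the week-24 EMR abstraction as a source for the exploratory overdose aim.

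The cost is wording and one further model run on records already being abstracted. The drawbacks should be stated with the results: care and deaths outside the health system will be missed, positives are sought more widely than negatives (which can raise apparent incidence and disturb calibration), and some overdose codes may not reflect misuse. Showing both analyses lets the reader judge how much these matter.
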